### Statistical analysis

Data analysis will be undertaken blinded to allocation. Analysis and presentation of data will be in accordance with Consolidated Standards of Reporting Trials (CONSORT) guidelines and in particular the extension to cluster randomized trials
[35]. The primary comparative analyses will be conducted on an intention-to-treat (ITT) basis with due emphasis placed on confidence intervals for the between-arm comparisons. Descriptive student- and class-level statistics will be used to ascertain any marked imbalance between the arms at baseline.

The primary analysis will employ a mixed effect linear regression model to compare the active CBT interventions (health- and school-led) versus treatment, adjusting as usual for stratification variables and baseline score, and taking appropriate account of the hierarchical nature of the data (repeated measures, children, classes and schools). Sensitivity analyses making different assumptions will be conducted to investigate the potential effects of missing data.

The extent of missing data will be reported and baseline factors will be compared for completers and non-completers to assess the extent of any bias that may result. Analysis will be undertaken using intention to treat (ITT). The potential for bias, dependent on the extent of missing data, will be assessed. Using the framework specified by White *et al.* an appropriate approach will be used to impute missing values in both outcome and descriptor variables
[36]. A further complete case analysis may also be undertaken and compared to the intention to treat results.

Secondary analyses will include: 1) repeating the primary analysis adjusting for any variables exhibiting marked imbalance at baseline to examine whether this influences the findings; 2) comparison of children who score high (that is, top 10% of total RCADS scores in each trial arm) and low on anxiety and mood at baseline (that is, remaining 90%) to examine who most benefits from these interventions; 3) similar analyses for other secondary outcomes (using appropriate multi-level models and adjusting *P* values for multiple testing); 4) investigation of process measures such as number of sessions attended; and 5) investigation of possible treatment moderators (for example, gender) and mediators (for example, school pedagogic orientation). Finally, although the study is not sufficiently powered to detect a difference between the two FRIENDS arms (school- and health-led) an exploratory analysis will be undertaken.

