**Discussion:**

As of September 2011, 41 schools have been recruited and randomized. Final 12-month assessments are scheduled to be completed by May 2013.

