## Methods/Design

### Aim of the study

The study has two primary aims:

1. To examine whether a school-based CBT program (FRIENDS delivered by either school or health professionals) is more effective than the usual school curriculum in reducing symptoms of anxiety and low mood in 9- and 10-year-old children (secondary prevention). Total Revised Child Anxiety and Depression Scale (RCADS) scores at baseline and 6 months will be compared for all children. A secondary analysis of the 10% of children in each arm who have the highest total RCADS scores will be undertaken to determine the effect upon the most symptomatic children.

2. To examine the effectiveness of FRIENDS in maintaining good emotional health, that is, to prevent high levels of anxiety and low mood from developing (primary prevention). Total RCADS scores at baseline and 12 months will be compared for the 90% of children who are not the most highly symptomatic.

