### Ethical approval and consent

The study was approved by the Department for Health Research Ethics Committee at the University of Bath. Consent/assent involves three stages. First, eligible schools were provided with information about the study and interested head teachers were required to provide written confirmation that their school wished to participate. Second, information was posted to the home address of the parents of all eligible children. Parents were invited to return a form opting out of the study if they did not wish their child to complete the study assessments. Finally, children were provided with information about the study and were required to provide signed assent before completing a baseline assessment. Dual carer/child consent/assent was therefore required for assessment completion.

The on-going conduct and progress of the trial is monitored by an independently chaired Data Monitoring and Ethics Committee (DMEC) and a Trial Steering Committee (TSC).

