### Study status

The trial started in January 2011 and 41 schools were randomized although one subsequently withdrew. Baseline assessments and intervention delivery started in September 2011 and twelve-month assessments are scheduled to be completed by May 2013.

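### High- and low-symptom groups are cut at the top 10% within each trial arm; one pooled baseline cut-off would remove avoidable chance imbalance at no cost

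*Protocol article*

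**What the plan says.** The rule appears in two places in the protocol article. Under Aim of the study, Aim 1 says "A secondary analysis of the 10% of children in each arm who have the highest total RCADS scores will be undertaken". Under Statistical analysis, the second secondary analysis is a "comparison of children who score high (that is, top 10% of total RCADS scores in each trial arm", set against the remaining 90%, with scores taken at baseline; its purpose is to see who benefits most.

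Aim 2 concerns the complement: "Total RCADS scores at baseline and 12 months will be compared for the 90% of children who are not the most highly symptomatic". It does not repeat the words about each arm, but the article offers no other definition of the most symptomatic children. The section opens with "The study has two primary aims", so Aim 2 is one of the primary aims. No common percentile and no fixed RCADS score is given anywhere.

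The primary model under Statistical analysis adjusts for baseline score. The second secondary analysis does not restate its model.

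**The concern.** A subgroup in a randomized comparison should be defined by a characteristic that is read the same way in every arm. A percentile taken separately in each arm makes membership depend on the child's score and also on the arm. With 40 schools over three arms, the three 90th percentiles will differ by chance. Children whose scores lie between the lowest and highest cut-off are then labelled high in one arm and low in another. The two FRIENDS arms, which the primary analysis sets together against usual PSHE, would carry two different definitions of high.

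Any baseline difference between arms also passes in full into both groups, because each arm's cut moves with its own distribution. The timing gives this some weight. The Discussion in the abstract says "As of September 2011, 41 schools have been recruited and randomized", Study status says "Baseline assessments and intervention delivery started in September 2011", and children "were required to provide signed assent before completing a baseline assessment". The scores that set the cuts therefore appear to be collected after schools were allocated.

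At stake are the meaning of the high group and the precision of any unadjusted comparison within the two groups. The statement about who benefits is affected too.

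**Working it through.** The article gives no figure for this rule, so there is none to reproduce. The check asks how far the cut-offs differ and what that does to the comparison.

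**Inputs from the article.** 40 schools and 1,448 eligible children (School recruitment); ICC 0.02, 90% consent, SD 12 and a target difference of 3.6 points (Power calculation).

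**Assumptions.** Children with a baseline score per school: 1,448 / 40 × 0.9 = 32.6, taken as 33, or about 1,320 in all and 440 per arm. Scores are normal unless stated. Schools per arm are not given; near-equal splits such as 14/14/12 are used. The baseline-to-follow-up correlation is set at 0.6.

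**Step 1: sampling error of one arm's cut-off.** The normal density at the 90th percentile is φ(1.2816) / 12 = 0.1755 / 12 = 0.01462 per point. Ignoring clustering, SE = √(0.1 × 0.9 / 440) / 0.01462 = 0.98 points. For the indicator of being above the cut, the ICC is about 0.02 × 0.1755² / 0.09 = 0.0068. The design effect is 1 + 32 × 0.0068 = 1.22, and the SE becomes 0.98 × √1.22 = 1.08 points.

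**Step 2: difference between arms.** For two arms the SD is 1.08 × √2 = 1.53 points. The expected range of three independent normal values is 1.693 SDs: 1.693 × 1.08 = 1.83 points. Simulation of the clustered trial gives an SD of about 1.5 and a mean range of 1.8 to 1.9, depending on the arm split. About 14 of 1,320 children (14 / 1,320 = 1.1%) change group compared with a pooled cut, where the high group holds about 132 children.

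**Step 3: effect on the FRIENDS-minus-usual-PSHE comparison, no treatment effect, no true baseline difference** (SD over simulated trials, points):

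| Quantity | Cut in each arm | One pooled cut |
|---|---|---|
| Baseline difference, high group | 1.48 | 0.94 |
| Baseline difference, remaining 90% | 0.90 | 0.74 |
| Follow-up difference, unadjusted, high group | 2.04 | 1.93 |
| Follow-up difference, baseline-adjusted, high group | 1.81 | 1.81 |
| Follow-up difference, baseline-adjusted, remaining 90% | 0.74 | 0.73 |

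The mean of each difference is close to 0 under both rules. The unadjusted row used 13/14/13 schools with 32 children each.

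**Step 4: less favourable cases.**
- Right-skewed scores: the SD of the cut-off difference rises to 2.3 points (95% within 4.4). The unadjusted high-group SD is 2.68 against 2.32 in one skewed form and 3.28 against 3.12 in another.
- A true baseline difference of 0.2 SD between FRIENDS and control (assumed; 0.2 × 12 = 2.4 points): the within-arm rule carries about 2.4 points into each group. The pooled rule leaves 0.4 in the high group and 1.7 in the remaining 90%. The mean unadjusted follow-up difference with no treatment effect is 1.5 against 0.3 points (high) and 1.4 against 1.0 (remaining 90%). After baseline adjustment it is close to 0 under either rule.

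**The case against.** The strongest reply is that nothing of consequence happens in the type of model the trial plans. With baseline score in the model and a linear relation to outcome, the treatment estimate in either group has the same mean and practically the same precision under both rules. About 1% of children move, and under randomization the expected cut-offs are equal. This stands, and it sets the severity. It does not defend the rule. The article attaches baseline adjustment to the primary analysis and does not restate it for the high/low comparison. The check assumes linearity, which matters most in the tail. Adjustment also cannot make high mean the same thing across arms.

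Three stronger readings are tempting and go beyond the documents.
- A reader might infer systematic bias because baseline scores follow allocation. Nothing in the article shows that assent or completion differed by arm; the timing only leaves the possibility open.
- A reader might infer that primary Aim 2 is invalidated. Aim 2 is reached only by implication, as the complement of the 10% in each arm, and its adjusted estimate is essentially unchanged.
- A reader might infer that high and low children will be compared on change regardless of arm, so that regression to the mean would pass for benefit. The article does not say so. With a control arm, the natural reading is a treatment effect in each group, where regression to the mean cancels between arms. Whether an interaction term is fitted is detail an article may leave to the analysis plan.

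**Conclusion.** The rule is stated twice and is a poor choice: it gives the subgroup a different definition in each arm and has no offsetting benefit. Its size is modest. The cut-offs span about 1.8 to 1.9 points on average, roughly half the 3.6-point target. Chance baseline imbalance rises from about 0.9 to 1.5 points (SD) in the high group, and from 0.74 to 0.90 in the remaining 90%. These figures rest on normal scores, about 33 assessed children per school and near-equal arms, all assumed.

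The result is extra chance imbalance, not bias, and baseline adjustment removes nearly all of its effect on within-group estimates if the outcome is linear in baseline. It matters more if the groups are compared unadjusted, if scores are skewed or the baseline relation is non-linear, or if arms really differ in the baseline scores collected after allocation. Severity is moderate to minor. This is an improvement worth making, not a fault that undermines the trial.

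**What to change.** Define high and low by a single cut-off: the 90th percentile of baseline total RCADS over all children in all three arms, computed blind to allocation. State this definition under Aim of the study and under Statistical analysis, and use it for both the top-10% analysis and Aim 2. Say explicitly that these analyses keep the adjustment for baseline score. Assess who benefits by an arm-by-baseline-RCADS interaction in the full mixed model, and report the high and low estimates alongside it.

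The cost is a few sentences; the data collected are the same. A pooled cut-off needs no arm labels, which suits the planned blinded analysis. The only downside is that each arm no longer contributes exactly 10% of its children to the high group, and the comparison does not need it to.

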**Methods/Design:**

The study is designed to be a pragmatic cluster randomized controlled trial evaluating the effectiveness of an efficacious school-based cognitive behavior therapy (CBT) prevention program (FRIENDS) on symptoms of anxiety and low mood in children 9 to 10 years of age. The unit of allocation is schools which are assigned to one of three conditions: school-led FRIENDS, health-led FRIENDS or treatment as usual. Assessments will be undertaken at baseline, 6 months and 12 months. The primary outcome measure is change on the Revised Child Anxiety and Depression Scale. Secondary outcome measures assess changes in self-esteem, worries, bullying and life satisfaction. An economic evaluation will be undertaken.

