### School recruitment

A list of 268 primary schools in Bath and North East Somerset, and in Swindon and Wiltshire was compiled from Local Authority information. Project information sheets were sent to the head teachers and meetings arranged with the 45 (17%) schools who expressed interest. Four schools did not return signed letters confirming participation before randomization and were therefore excluded. A total of 41 schools were randomized with one school withdrawing after randomization. The cohort therefore consisted of 40 schools (1,448 eligible children).

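### The high-symptom group is cut at the top 10% within each arm, so the subgroups rest on up to three different baseline RCADS scores instead of one trial-wide cut-off

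*Protocol article*

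**What the plan says.** Under Statistical analysis, the second of the listed secondary analyses compares children who score high and low at baseline. High means the "top 10% of total RCADS scores in each trial arm"; low means the remaining 90%. The stated purpose is to learn who gains most from the interventions.

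Aim of the study gives the same rule under Aim 1: "A secondary analysis of the 10% of children in each arm who have the highest total RCADS scores will be undertaken". Aim 2 then says: "Total RCADS scores at baseline and 12 months will be compared for the 90% of children who are not the most highly symptomatic". That sentence does not itself repeat that the split is made by arm. The link is that its 90% is the complement of a 10% that is defined by arm in both sections. The section introduces both aims with "The study has two primary aims".

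No fixed or common RCADS threshold appears anywhere in the article. The balancing variables under Randomization are school and class characteristics and attainment; baseline RCADS is not among them. The primary model under Statistical analysis adjusts for baseline score.

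**The concern.** A subgroup compared between randomised arms should be formed by one rule that treats every child alike. Here membership depends on the child's own score and also on the score distribution of the arm to which the school was allocated. Two children with the same baseline total can be high in one arm and low in another.

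Two consequences follow. First, the result has no single severity attached to it, so it cannot say at which RCADS score a child falls into the group that benefits more or less. The main contrast sets both FRIENDS arms together against usual PSHE, so even the FRIENDS side of the high group mixes two cut-offs. Second, any baseline difference between arms passes straight into the subgroup: the arm with higher scores gets the higher cut-off and the more severe high group. One common cut-off would remove most of that difference within the high group.

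**Working it through.** **Inputs from the protocol article.** 40 schools and 1,448 eligible children (School recruitment); 90% consent, SD 12, ICC 0.02 (Power calculation). The target difference reproduces: 0.3 × 12 = 3.6 points. The article gives no figure for the 10%/90% split.

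**Size of the groups.** 1,448 × 0.90 ≈ 1,303 children with a baseline. High group: 1,303 × 0.10 ≈ 130, or about 130 / 3 ≈ 43 per arm.

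**Assumed, because the article is silent.** 33 children per school; schools split 13/13/14 or a near equivalent; whole-number scores from 0 to 90 with mean about 24 to 25; either a normal or a right-skewed (gamma) shape.

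**How far the cut-offs differ.** In each of 2,000 simulated trials with no true difference between arms, the top-10% cut-off was found in each arm and compared with one pooled 90th percentile. At ICC 0.02:

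| Quantity | Normal | Skewed |
|---|---|---|
| Trials in which the three cut-offs are not all equal | 93% | 96% |
| Mean gap, highest minus lowest cut-off | 1.9 | 2.6 |
| 95th percentile of the gap | 4 | 5 |
| Children whose score is high in one arm and low in another | 2.9% | 2.8% |
| SD of FRIENDS-control baseline difference in the high group, arm-wise cuts | 1.56 | 2.41 |
| The same SD with one pooled cut | 0.92 | 1.49 |

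Over ICC 0 to 0.05, the first row ranges from 90% to 97%. About 3% of 1,303 is some 37 to 38 children. A separate simulation gave a mean gap of 1.8 to 2.4 points, and SDs of about 1.5 to 2.3 (arm-wise) and 0.9 to 1.5 (one cut).

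**Does this reach the treatment effect?** Suppose that FRIENDS schools start 2 points higher, that the slope of follow-up on baseline is 0.6 and the same line holds in all arms, and that there is no treatment effect (all assumed). The unadjusted change-score artefact is the baseline difference × (1 − 0.6).

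- High group, arm-wise cuts: baseline difference about 2.0, so 2.0 × 0.4 = 0.8 points in favour of FRIENDS.
- High group, one cut: baseline difference 0.2 to 0.35, so 0.08 to 0.14, about 0.1 point.
- Lower 90%, arm-wise cuts: 1.9 to 2.0, so about 0.76 to 0.80.
- Lower 90%, one cut: 1.4 to 1.6, so about 0.56 to 0.64.

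With baseline score as a covariate, the mean null bias in the high group was −0.01 to 0.03 with arm-wise cuts and −0.02 with one cut. The SD of the estimate was 1.89 to 1.99 against 1.92 to 2.11. In the lower 90% the adjusted bias was at most 0.05 in absolute size under both rules. With a slope that flattens at high scores, the bias stayed within 0.1 point.

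**How likely is a 2-point shift by chance?** Design effect: 1 + 32 × 0.02 = 1.64. With 27 FRIENDS schools (891 children) and 13 control schools (429), the SD of the baseline mean difference is √[144 × 1.64 × (1/891 + 1/429)] ≈ 0.90. A shift of 2 points is 2 / 0.90 ≈ 2.2 SD, reached in about 3% of trials counting both directions.

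**The case against.** The strongest defence is that nothing in the planned inference is distorted. The primary analysis uses all children and is untouched. Under randomisation the imbalance averages zero. The baseline adjustment in the primary model removes what chance leaves, with about the same precision under either cut. All of this stands.

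A reader might go further than the documents allow in three ways.

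- **That the rule builds in a spurious FRIENDS benefit of about 0.8 points.** That figure needs an unadjusted change score and an assumed 2-point head start, which chance alone seldom produces. The article plans adjustment for baseline.
- **That a primary aim is compromised.** The Aim 2 sentence does not say that the split is by arm, only about 3% of children are affected, and one cut-off would remove little of the unadjusted artefact (about 0.8 falls to about 0.6). What remains is ordinary imbalance between arms. Statistical analysis also lists the high/low comparison as secondary.
- **That a gap of 2 to 2.5 points can be read against the 3.6-point target.** The first is a gap between cut-offs; the second is a difference in outcome.

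The defence does not cover everything. The item on high and low scorers does not restate the baseline-adjusted model, and Primary outcome measures describes the outcome in terms of change, so an unadjusted reading is not excluded. Randomization and Study status suggest that baseline assessments followed allocation, so differences in who completes them are possible. The lack of a single score to which the subgroup result applies is not answered at all; the only gain from the arm-wise rule is an equal 10% share in each arm.

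**Conclusion.** The concern holds as a defect of definition and interpretation. Ranking within arms will very probably give different cut-offs, about 2 to 2.5 points apart on average, and about 3% of children would be classed differently depending on their arm. It also makes chance baseline imbalance in the high group more than half as large again as it need be (1.56 / 0.92 ≈ 1.7; 2.41 / 1.49 ≈ 1.6). These sizes rest on the protocol's SD and ICC and on assumed score shapes and school split. Because scores are whole numbers, the cut-offs could coincide.

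It does not amount to a material bias in the planned analysis. With baseline adjustment the bias is about zero, provided that follow-up is roughly linear in baseline on a line common to the arms. The consequence for Aim 2 is small.

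**What to change.** In Aim of the study and in the second listed secondary analysis under Statistical analysis, replace the by-arm wording with one trial-wide cut-off. This can be the 90th percentile of baseline total RCADS over all children with a baseline, computed before arm codes are attached, or one fixed score set in advance. Apply that score alike in all three arms, for the high group and for the lower group used in Aim 2. Add that the subgroup comparisons use the same baseline-adjusted mixed model as the primary analysis.

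The cost is wording only: no new data are needed, and forming the groups no longer needs arm labels, which suits the planned blinded analysis. The one drawback is that the high group will not be exactly 10% in every arm.

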### Economic evaluation

The analysis of the cost data, the CHU-9D data and cost-effectiveness analysis will be conducted according to current best practice methods for conducting economic evaluation alongside trials,
[37,38] and specifically alongside cluster-randomized controlled trials
[39]. Incremental costs, incremental effects, and where relevant incremental cost-effectiveness ratios (ICERs) will be estimated, comparing the three conditions. The incremental cost per unit quality-adjusted life year (QALY) increase will be estimated. Both unadjusted analyses and adjusted analyses will be carried out, adjusting for site, mode of delivery, number of students and number of classes.

Random effects bivariate linear regression models will be fitted to model cost and effectiveness (QALY) simultaneously, allowing for correlation within clusters and correlation between cost and effectiveness score within participants
[40]. From these models we will estimate: the mean difference in costs of the three conditions and corresponding standard error; the mean difference in effect and corresponding standard error; and, indirectly via the variance-covariance matrix of the regression coefficients, the correlation between the mean cost difference and the mean effect difference. Where the interventions are estimated to have both higher costs and greater effectiveness than control, we will use Fieller’s method to obtain a parametric estimate of the 95% confidence interval for the ICER and to construct the cost-effectiveness acceptability curve (CEAC). Both parametric and non-parametric bootstrap estimates of the confidence interval for the ICERs will be estimated.

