### Randomization

Allocation of schools took place once all schools had been recruited. Balance between trial arms with respect to key characteristics (school size, number of classes, numbers of children in year 5 classes, preferred term of delivery, preferred day of delivery, mixed-year 5 classes (that is, classes that were year 4 and year 5 combined and classes that were year 5 and year 6 combined) or single year 5 classes and level of educational attainment) was achieved by calculating an imbalance statistic for a large random sample of possible allocation sequences
[22]. A statistician with no other involvement in the study randomly selected one sequence from a subset with the most desirable balance properties.

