### Outcomes for the economic evaluation

In order to assess cost-utility, all children will complete the Child Health Utility-9D (CHU-9D) at baseline and at 6 and 12 months
[33]. The CHU-9D, a validated measure of pediatric health-related quality of life, is short (nine items) and has been specifically developed for use with children aged 7 to 11 years. The use of the CHU-9D will allow us to assess how improvements in mental health (anxiety and depression) translate into changes in overall health-related quality of life.

For collecting health, social care and educational resource use data, structured interviews will be conducted with a sample of carers/parents for each of 300 children, with approximately 100 children from each of the three conditions. All parents will be invited to participate and they will be offered £20 to cover the cost of their time. They will complete the Client Receipt of Services Questionnaire, a structured interview that assesses their child’s use of social, health and educational services over the past 6 months
[34]. In addition, a screen of parental health and mental health, assessment of life events and a survey of child leisure and sport activities will be undertaken.

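### The covariate list for the adjusted economic analysis omits baseline CHU-9D, which every child is to complete, so the incremental QALY and ICER lose precision and carry chance baseline imbalance

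*Protocol article*

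**What the plan says.** The Economic evaluation section commits to two versions of the analysis and names the adjustment set for one of them: "Both unadjusted analyses and adjusted analyses will be carried out, adjusting for site, mode of delivery, number of students and number of classes". The four variables describe the school or the delivery; none is a measurement on the child. The next paragraph gives the model, "Random effects bivariate linear regression models will be fitted to model cost and effectiveness (QALY) simultaneously", with clustering and the cost-effect correlation allowed for, and adds no further covariate. The section does not say whether the adjusted or the unadjusted version is the base case.

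The missing covariate will exist. Under Outcomes for the economic evaluation, "all children will complete the Child Health Utility-9D (CHU-9D) at baseline and at 6 and 12 months".

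Elsewhere the article does adjust for a baseline value. The primary RCADS model in the Statistical analysis section is fitted "adjusting as usual for stratification variables and baseline score". That sentence concerns the primary clinical model, and the economic section does not carry it over.

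**The concern.** A child's utility at baseline usually predicts that child's utility six and twelve months later, and under the usual calculation it is also one of the components of the QALY. Leaving it out of the effect equation has two consequences. Variance that a collected covariate could explain stays in the residual, so the interval for the incremental QALY is wider than it need be. And if the arms happen to differ in baseline utility, part of that difference is reported as a difference in QALYs.

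Nothing in the design balances baseline utility directly. Allocation was constrained on school characteristics such as "school size, number of classes, numbers of children in year 5 classes, preferred term of delivery, preferred day of delivery", together with class structure and educational attainment.

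What is at stake is the economic conclusion, not the primary RCADS result. The sign of the estimated effect also matters procedurally: the article reserves Fieller's interval and the acceptability curve built from it for the case where the interventions are estimated to be both more costly and more effective than control.

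**Working it through.** **No figure to reproduce.** The article gives no expected incremental QALY, CHU-9D SD or between-visit correlation. The calculation below is therefore an illustration under assumptions, shown as ranges.

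**Inputs from the article.** CHU-9D at 0, 6 and 12 months (Outcomes for the economic evaluation). 40 schools and 1,448 eligible children, so 1,448/40 = 36.2 per school (School recruitment). ICC 0.02, 90% consent and 80% retention (Power calculation; the ICC was set for the clinical outcome and is borrowed here).

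**Assumptions not in the article.** Area-under-the-curve QALY over 12 months; equal utility SD *s* at each visit, 0.10 to 0.15; the same correlation *r* between any two visits, 0.3 to 0.7; 13 control schools against 14 in one FRIENDS arm; baseline equally predictive at child and school level.

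**Step 1: weights.** The trapezoid rule gives QALY = 0.25·u0 + 0.50·u6 + 0.25·u12.

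**Step 2: dependence on baseline.**
- Slope of QALY on u0 = 0.25 + 0.75r
- Var(QALY) = (0.375 + 0.625r)·s²
- R² = (0.25 + 0.75r)² / (0.375 + 0.625r)
- Proportional fall in SE = 1 − √(1 − R²)

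| r | Slope | Var/s² | R² | Fall in SE | QALY shift per 0.01 of baseline imbalance |
|---|---|---|---|---|---|
| 0.3 | 0.475 | 0.5625 | 0.40 | 23% | 0.0048 |
| 0.5 | 0.625 | 0.6875 | 0.57 | 34% | 0.0063 |
| 0.7 | 0.775 | 0.8125 | 0.74 | 49% | 0.0078 |

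**Step 3: how large a chance imbalance might be, using all children.**
- Analysed children per school: m = 36.2 × 0.9 × 0.8 = 26.06
- Design effect: 1 + 25.06 × 0.02 = 1.50
- Arm sizes: 13 × 26.06 = 339 and 14 × 26.06 = 365
- SE of the baseline difference: s·√(1.50 × (1/339 + 1/365)) = 0.092·s, which is 0.009 for s = 0.10 and 0.014 for s = 0.15

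A one-SE imbalance then moves the incremental QALY by 0.0044 (s = 0.10, r = 0.3) to 0.0107 (s = 0.15, r = 0.7). Of this, 0.0023 to 0.0035 comes through the 0.25 weight alone, and the rest through persistence into later visits. With an ICC of 0.05 the range is 0.0054 to 0.0132.

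**Step 4: precision in absolute terms.** With s = 0.10, r = 0.5 and ICC 0.02, the SE of the QALY difference is √0.6875 × 0.0092 = 0.0077 without baseline, and 0.0077 × √(1 − 0.568) = 0.0050 with it.

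**The case against.** **The list may not be closed.** It does not say that only these variables will be used. One of them, mode of delivery, appears to overlap the school-led and health-led allocation itself, which suggests a loose summary. The section also opens with a general commitment: "The analysis of the cost data, the CHU-9D data and cost-effectiveness analysis will be conducted according to current best practice methods". A fuller economic plan could include baseline utility. This stands in part: the article does not refuse the adjustment. But the general sentence does not name baseline utility and the specific list follows it, so an analyst working from the article would leave it out.

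**The QALY construction is assumed.** This stands. If only follow-up utilities were used, imbalance would still carry through the correlation, with different numbers. If change from baseline were used, the shifts above would not apply.

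**Chance imbalance is already in the interval.** This also stands. The unadjusted estimator and its SE are valid under randomization, so the loss is one of precision and of error in the realised estimate. A reader might infer bias, or that imbalance passes into the QALY one for one. Neither follows: on the assumptions above the share is about 0.5 to 0.8.

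**Two stronger readings are tempting.** The first is that the QALY comparison rests on about 100 children per arm, which would make imbalance larger. That number is the parent-interview sample for resource use; the article has all children complete the CHU-9D and does not restrict the QALY analysis to the sample. The second is that imbalance alone will reverse the sign of the result. That needs an expected incremental QALY, which the article does not give.

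**Other safeguards.** Constrained allocation on school characteristics and the planned inspection of baseline imbalance help somewhat. The former does not balance utility directly, and the re-analysis for marked imbalance is specified for the primary analysis only.

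**Conclusion.** The point holds as a free improvement to a secondary analysis. The article lists the covariates of the adjusted economic analysis and omits a baseline measure that is collected from every child and expected to predict the QALY strongly. Under an area-under-the-curve QALY, equal SDs and between-visit correlations of 0.3 to 0.7, adding it would cut the SE of the incremental QALY by about 23% to 49% and remove an expected shift of about 0.005 to 0.008 QALY per 0.01 of baseline imbalance. Whether that changes the size or sign of the ICER depends on the true QALY difference being small, which the article neither states nor excludes. The omission itself is plain from the text; its size rests on assumed correlations, SDs and QALY construction.

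**What to change.** State how the QALY is calculated from the three CHU-9D assessments. Add baseline CHU-9D utility as a child-level covariate in the QALY equation of the adjusted bivariate cost/QALY model, name that model as the base case, and keep the unadjusted result as a sensitivity analysis. Settle this before the outcome data are analysed, so that the choice between adjusted and unadjusted ICERs is not made once results are known. The cost is one covariate that the trial already collects; it needs no extra data collection and no change to the design.
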